### Abstract

#### Background

Loneliness is one of the most prevalent global mental health problems among older adults and has become particularly concerning during the COVID-19 pandemic with constraints on social engagement. To reduce loneliness in older adults, we will examine the effectiveness of two telephone-delivered loneliness interventions (i.e., behavioral activation based on the behavioral theory of depression and mindfulness based on the monitor and acceptance theory) against a telephone-delivered befriending intervention as an active control. To meet the demand for loneliness-reducing interventions and enhance sustainability and scalability, retirees are recruited and trained as volunteers to implement these interventions.

#### Methods

In a three-arm randomized controlled trial, older adults in Hong Kong who live alone and under the poverty line, do not have Internet at home, and feel lonely will be randomly assigned to receive one of the three interventions (enrollment goal,  $N = 966$ ). The primary outcomes will be loneliness, social network indicators and perceived social support. Secondary outcomes will be perceived stress, sleep quality, anxiety and depressive symptoms, physical and cognitive health. Underlying mechanisms will be examined with mindfulness, activity happiness/meaningfulness, diurnal cortisol patterns, levels of the salivary C Reactive Protein, and genetic markers (candidate gene, GWAS, biological pathway related SNPs, and polygenic risk scores).

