### Study Objectives and Hypothesis

The COVID-19 pandemic has undoubtedly imposed a wide range of restrictions on older adults' participation in social activities, increasing their level of loneliness. Low-income older adults who live alone and have limited access to the Internet are at higher risk of loneliness (52,53). Our primary aim is to evaluate whether a Tele-Behavioral Activation (Tele-BA) and a Tele-Mindfulness (Tele-MF) intervention are more effective than the active control consisting of Tele-Befriending (Tele-BF) in reducing loneliness (i.e., one of the primary outcomes, see below for details on all measures) among community-dwelling older Chinese adults in Hong Kong who live alone and in poverty and have limited access to the Internet. Tele-BA focuses on increasing and reinforcing a target individual's engagement in meaningful life activities (31), Tele-MF focuses on increasing awareness of the present moment with acceptance (20), whereas Tele-BF refers to a volunteer's provision of emotional support for the target individual who reports loneliness (50). We hypothesize that Tele-BA and Tele-MF interventions are effective in reducing perceived loneliness, measured at the 4-week, 3-month, 6-month, and 12-month follow-up assessments, compared to Tele-BF group.

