## Supplement 1. Study Protocol

### Sample Size

A required sample size for the RCT on loneliness was estimated for one of the primary outcomes, that is, loneliness assessed by UCLA Loneliness Scale (54). A previous intervention study on reducing loneliness in older adults yielded an effect size of 0.5 (31). To be more conservative, we estimate the sample size based on a smaller effect size, i.e., 0.25. To detect an effect size of 0.25 at an alpha error rate of 0.05 and a power of 90%, the estimated sample size is 289 participants in each group. With an anticipated drop-out rate of 10% over a period of 6 months, the necessary sample size is 322 participants per group at baseline ( $N=966$  in total).

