### **Primary Outcomes**

Table 1 shows an overview of timeline and measures. Loneliness and perceived social support are the primary outcomes of the intervention.

**Loneliness.** Loneliness is measured by the De Jong Gierveld Loneliness Scale (56) and the 20-item Revised UCLA Loneliness Scale (58). The validated Chinese version of the De Jong Gierveld Loneliness Scale (Leung et al., 2008), consisting of six items, is adopted to measure retrospective loneliness. Participants are asked to indicate their level of agreement with the six statements on a 3-point scale (1 = yes, 2 = more or less, 3 = no). Sample items include “I experience a general sense of emptiness,” “Often, I feel rejected,” and “I miss having people around.” Means and standard deviations will be used in data analysis. The statements will be reversely scored with higher values representing higher loneliness.

The Revised UCLA Loneliness Scale (58) comprises 20 items to assess loneliness and has been validated among Chinese adolescents (59). This version improved from the original UCLA Loneliness Scale (60) by addressing concerns on the direction of the items, discriminant validity, social desirability (58). Each

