## Supplement 1. Study Protocol

item in the Revised UCLA Scale is a question starting with “How often do you feel?” Participants are asked to indicate how often they think each question describes their experiences on a 4-point scale (1 = never to 4 = always). Sample items include “How often do you feel alone?”; “How often do you feel that there is no one you can turn to?”; and “How often do you feel that you are no longer close to anyone?”. Items are averaged with higher score indicating higher perceptions of loneliness.

**Perceived Social Support.** Perceived social support is assessed using the Chinese version of the 12-item Multidimensional Scale of Perceived Social Support (MSPSS) (61,62). The MSPSS asks participants to indicate their level of agreement with 12 items on a 7-point scale (1 = strongly disagree to 7 = strongly agree). Sample items include “I get the help and support I need from my friends,” “I get the emotional help and support I need from my family,” and “My family is willing to help me make decisions.” Answers on all 12 items will be averaged to derive a total score of perceived social support, with higher values representing higher perceived social support.

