### Secondary Outcome Measures

The secondary outcomes include social network size, psychological well-being, life satisfaction, stress level, sleep quality, symptoms of depression and anxiety, physical health, and cognitive health.

**Social network size.** Social network size is assessed using the Chinese validated Lubben Social Network Scale (57,63). The Lubben Social Network Scale consists of two sets of three questions. The first set evaluates the kinship ties of participants: “How many relatives do you see or hear from at least once a month?”; “How many relatives do you feel close to, such that you could call them for help?”; and “How many relatives do you feel at ease with that you can talk about private matters?” The second set evaluates the non-kin ties of participants by asking three parallel questions. The only difference is that the word *relatives* is replaced with the word *friends*. Participants indicate the number of social partners on a 6-point scale (0 = none to 5 = more than 9 people), deriving in sum scores representing larger network sizes for a total of relatives/friends as well as for friends and family separately.

**Psychological Well-being.** Participants' psychological well-being is assessed using the Psychological Well-being Scale, originally developed by Ryff and colleagues (64). In this study, we utilize the validated brief version of the scale specifically tailored for the Hong Kong Chinese population, as validated by Chan, Chan, and Sun in 2017 (65). The scale consists of six dimensions of psychological functioning including autonomy (e.g., “have confidence in one’s opinions”), environmental mastery (e.g., “No difficulty in arranging life”), personal growth (e.g., “Have developed a lot as a person”), positive relations with others (e.g., “Enjoy conversations with friends”), purpose in life (e.g., “Enjoy making plans for the future”), and self-acceptance (e.g., “Feel good about self”). Participants will be asked to rate to what extent they agree with each of the statement on a 6-point scale (1 = strongly disagree to 6 = strongly agree).

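### The protocol gives two different primary outcome sets, ranks no loneliness scale first, and sizes the trial at one undivided alpha of 0.05 for only one of the primary outcomes

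*Protocol*

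**What the plan says.** Three sections of the protocol define the outcome set.

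- Abstract, Methods: "The primary outcomes will be loneliness, social network indicators and perceived social support". Its list of secondary outcomes does not mention social network.
- Primary Outcomes: "Loneliness and perceived social support are the primary outcomes of the intervention".
- Secondary Outcome Measures: "The secondary outcomes include social network size, psychological well-being, life satisfaction", followed by further measures.

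The Primary Outcomes section assigns two instruments to loneliness, the six-item De Jong Gierveld scale and the 20-item Revised UCLA scale, and ranks neither first. Perceived social support is the MSPSS total. Social network is the Lubben scale, scored in total and separately for friends and family.

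The Sample Size section says its calculation was "estimated for one of the primary outcomes, that is, loneliness assessed by UCLA Loneliness Scale". It assumes an effect of 0.25, alpha 0.05 and 90% power, giving 289 per group, or 322 after 10% dropout over 6 months (966 in total).

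Study Objectives and Hypothesis covers both active arms in one statement, "We hypothesize that Tele-BA and Tele-MF interventions are effective in reducing perceived loneliness", against befriending at four follow-ups. The planned analysis takes the Group × Time interaction in a mixed model for loneliness as the measure of effect. It does not say which loneliness scale that is.

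**The concern.** Any analysis plan written for this protocol must contradict either the abstract or the body, because social network cannot be both primary and secondary. While both statements stand, the outcome could be reported at either level once results are known.

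The second issue is the error rate. The Sample Size section sets alpha as if one scale and one comparison decided the trial, yet it describes that scale as only one of several primary outcomes. With three or four primary scales and two active arms, 5% describes each test and not the trial's claim as a whole. A later correction would draw on power that was never budgeted.

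**Working it through.** **1. Counting the primary scales.**

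| Source | Loneliness | Support | Network | Primary scales |
|---|---|---|---|---|
| Primary and Secondary Outcome sections | 2 | 1 | secondary | 3 |
| Abstract | 2 | 1 | 1 | 4 |

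Each scale carries two comparisons with befriending: 3 × 2 = 6 or 4 × 2 = 8.

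**2. The plan's own sample size.** For a two-sided comparison of two means with SD 1, n per arm = 2(z₁₋α/₂ + z₁₋β)² / 0.25².

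- 90% power: 2(1.960 + 1.282)² / 0.0625 gives 337, not 289. The one-sided version gives 275.
- 85% power: 2(1.960 + 1.036)² / 0.0625 gives 288 (289 with the t distribution).
- Dropout: 289 / 0.9 gives 322, and 3 × 322 = 966. This step reproduces.

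So 289 matches a single two-group comparison at an undivided two-sided 0.05 with about 85% power. No allowance for several scales or two comparisons is visible in it.

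**3. Chance of at least one false positive.** Each test is at two-sided 0.05 and any positive result is taken to count. For k independent tests the chance is 1 − 0.95^k. For correlated tests, multivariate normal statistics were simulated under the null. The correlation between the two comparisons is 0.5, which follows from a shared control and equal arms. Correlations between scales and between visits are assumptions; the protocol gives none.

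| Reading | Tests | Independent | Correlated |
|---|---|---|---|
| One scale, one time point, two comparisons | 2 | 9.75% | 9.0% |
| One Group × Time test per scale, 3 scales | 3 | 14.3% | 11–14% |
| One Group × Time test per scale, 4 scales | 4 | 18.5% | 13–17% |
| 3 scales × 2 comparisons, one time point | 6 | 26.5% | 17–24% |
| 4 scales × 2 comparisons, one time point | 8 | 33.7% | 20–30% |

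Correlations between scales run from 0.3 to 0.7 in the Group × Time rows and from 0.3 to 0.8 in the two rows below them. The Group × Time test was represented by one normal test per scale, which is an approximation. Its range, with independence as the upper end, is 11–19%.

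Testing each of the four visits separately would give 24 or 32 tests. With correlations of 0.3–0.7 between scales and 0.5–0.7 between visits, the chance is then 43–59% or 49–69%.

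**4. Power if alpha is divided.** With 289 per arm the standardised effect is 0.25 × √(289/2) = 3.005, and power = Φ(3.005 − z₁₋α/₂).

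- α = 0.05: Φ(3.005 − 1.960) = 85.2%
- α = 0.025: Φ(3.005 − 2.241) = 77.8%
- α = 0.05/6: 64.3%
- α = 0.05/8: 60.7%

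**The case against.** The strongest reply is that the certain defect is one phrase in the abstract. The body agrees with itself on social network, and the primary aim, sample size and effects analysis all centre on loneliness. Multiplicity rules and the order of contrasts commonly sit in a statistical analysis plan, which is not at hand. This largely stands: the absence of a multiplicity rule from the protocol is not held against it here. It does not remove the contradiction, the two unranked loneliness scales, or an alpha already spent undivided in the sample size. Even if loneliness alone counted, two scales with two comparisons each at one time point give 14–17%.

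A reader might infer that the trial runs a false-positive rate of 43–69%. The documents do not support that. The planned test is a Group × Time interaction that takes the visits together; four follow-ups are listed, but no separate test at each is planned. The figure is an upper bound across readings.

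A reader might also infer that any positive scale or arm would be declared a success. No such rule is written, and the error rates above are conditional on it.

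Finally, whether two distinct interventions compared with one control need a shared alpha is a matter of statistical position. Without that element, 11–19% from one test per scale remains.

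**Conclusion.** The concern holds. The contradiction between the abstract and the two outcome sections is certain and must be reconciled. The lack of a lead loneliness scale is equally plain from the text.

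The size of the error inflation is conditional. It is about 11–19% with the planned type of test applied once per scale, and about 17–30% with two comparisons per scale at a single time point. Both ranges assume 0.05 per test, any positive result counting, no correction elsewhere, and the stated correlations. No reading with more than one scale or comparison stays at 5% under those conditions.

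Two tempting details are not settled by the document. It does not say which UCLA version underlies the sample size: the reference cited there evaluates full, eight-item and three-item forms, the three-item form is used for eligibility, and the 20-item outcome carries a different citation. Nor does it name 6 months as the primary time point; that is the horizon for dropout only.

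**What to change.** Issue a dated amendment, made without sight of outcome data by arm, that does the following.

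1. Reconciles the abstract with the outcome sections, listing social network size as secondary in both.
2. Names one loneliness scale as the lead primary outcome. The UCLA scale is the natural choice because the size was set on a UCLA scale; the amendment should confirm that the 20-item version is meant.
3. States the deciding contrast or time point for that scale, and controls the overall two-sided 5% across Tele-BA versus Tele-BF and Tele-MF versus Tele-BF, for example with Hochberg's procedure. The De Jong Gierveld score and MSPSS then follow in a fixed order.

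Six months is a reasonable candidate because dropout was budgeted to that point. The sponsor should make the choice while blind to results by arm: recruitment closed on 30 April 2023 and follow-up runs to April/May 2024, so most 6-month data will exist before the 12-month data close.

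The change is wording only, but it costs power. With 289 per arm and an effect of 0.25, power per comparison is about 78% at two-sided 0.025, against about 85% at 0.05 and the 90% the protocol states. These figures are for a simple two-group comparison at one time point, before any gain from the repeated-measures model or baseline adjustment.

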#### Discussion

The findings are expected to provide robust evidence for the effectiveness of behavioral activation and mindfulness interventions to reduce loneliness and improve well-being among older adults in Hong Kong. Delivery via telephone facilitates scalability and sustainability and will allow large-scale implementations.

The study was prospectively registered in the Clinical Trials Registry of the University of Hong Kong Clinical Trials Centre (registration number: HKUCTR-2929) and retrospectively registered at the Chinese Clinical Trial Registry in the WHO Registry Network (number ChiCTR2300072909). The contents of the two registrations are identical.

## Supplement 1. Study Protocol

### Background

Loneliness is one of the most prevalent psychological problems among older adults globally. Studies have shown that loneliness affects more than 20% of older adults in China, Europe, and the United States (1–3). Loneliness in older adults is linked to various age-related risk factors, such as functional impairments in daily activities or social isolation (4), as well as to poor mental health outcomes, including depressive symptoms (Cacioppo et al., 2006) or suicidal ideation (6). The COVID-19 pandemic has aggravated risks for loneliness (7,8), since physical distancing measures aimed at reducing transmission of the SARS-CoV-2 virus restricted older adults' participation in social activities and reduced their contact with family members and friends. There is an urgent need to develop effective interventions to help reduce loneliness among community-dwelling older adults, especially those who live alone and have limited access to the Internet (i.e., social media connections) in future crisis situations.

Research has shown two effective approaches to reducing loneliness (9–11) that are grounded in theories of bipolarities of emotion and emotion regulation (12,13). The first approach focuses on improving positive affect (14,15) by increasing access to social interactions and social support and enhancing social skills via, for example, activity-based group interventions (16). An intervention strategy within this approach is Behavioral activation (BA). BA is designed to help individuals engage in meaningful and pleasant activities and to avoid aversive stimuli and has been found effective in reducing loneliness and depression in older adults (17,18). The second approach focuses on supporting individuals to better regulate negative emotions (e.g., stress and anxiety) triggered by loneliness (19,20) and making them aware of possible maladaptive cognitions in social situations (21). For example, mindfulness meditation interventions (MF) have been shown to be effective in reducing loneliness by guiding participants to focus on present-moment experiences, accept negative experiences, and remain equanimous (20). However, scientific evidence regarding the most effective approaches and their scalability and sustainability need to be firmly established (22). To address this research gap, we aimed at comparing these two approaches by examining the effectiveness of telephone-delivered BA and MF against simple befriending as an active control. Here we provide the protocol of the interventions and study design to test them.

### Behavioral Activation

Building on the behavioral explanations of learning theory, BA posits that symptoms of depression will decrease when one engages in positively reinforced daily activities (i.e., healthy behaviors) (23–26). BA is a brief, uncomplicated, and structured treatment of depression (25,27), and its effectiveness has been found to be comparable to the effect of cognitive behavioral therapy, but at a lower cost (28).

Because of its observed benefits in alleviating depressive symptoms, BA has also been applied to nonclinical samples. For example, using a non-age-specific sample, studies have demonstrated the effectiveness of BA in reducing participants' level of loneliness, both when BA is administered separately (29) or as part of a

## Supplement 1. Study Protocol

larger intervention package (30). BA has also been used to reduce loneliness in older adults (see Orgeta et al., 2017 for a meta-analysis). Choi and colleagues, for example, developed a videoconferencing BA program for low-income, housebound, lonely older Americans (31). The intervention consisted of five one-hour weekly sessions delivered remotely, with the aims of promoting engagement in activities aligned with older adults' personal values, reviewing their daily activity patterns, and planning and executing activity goals. Compared with the participants in the active control (friendly visit) group, the participants in the BA intervention engaged in more social interactions, felt more satisfied with social support, and reported lower levels of loneliness, depression, and disability (31). Similar intervention programs with BA features have also been shown to be effective in reducing older adults' loneliness and depressive symptoms in England and Wales (32) as well as in Sweden (33). To sum up, BA is designed to increase engagement in meaningful and pleasant activities through (a) behavior monitoring and activity planning; (b) the use of behavioral strategies such as relaxation, stress management, and mastery; and (c) the enhancement of social skills such as seeking social support from others (26,31).

### **Mindfulness Intervention**

MF interventions aim to cultivate participants' present-moment focus with acceptance and nonjudgmental awareness (20). This focus is particularly effective in regulating the negative emotions triggered by loneliness (34). MF interventions have been shown to be effective in improving interpersonal relationship skills and relationship quality (35), fostering emotional regulation (36) and compassion toward others (37), improving social relationship functioning in couples (38), and in reducing anxiety, depressive symptoms (39) and loneliness (40).

In a review of 15 MF interventions, Geiger and colleagues demonstrated the feasibility and acceptability of using MF interventions in older adults (41). This review highlights that all included studies found MF interventions to be effective in promoting physical and emotional well-being among older adults (41). However, few interventions have focused on loneliness and interpersonal outcomes in older adults. In a small randomized controlled trial (RCT) of 40 healthy older adults (19), the face-to-face Mindfulness-Based Stress Reduction (MBSR) program, consisting of eight weekly 120-minute group sessions, a day-long retreat, and a daily 30-minute home practice, reduced loneliness. Creswell et al. also showed a reduction in C-reactive protein (CRP) to a marginally significant level. Kwok et al. conducted a weekly 90-minute MF yoga intervention over 8 weeks in Hong Kong, and showed that this intervention was effective in reducing anxiety and depressive symptoms in adults with Parkinson's disease, most of whom were older adults (39). All of these interventions were delivered face to face. In another small-scaled feasibility study conducted in Hong Kong, Kwok et al. examined an eight biweekly 90-min home-based MF intervention delivered via video-conferencing software (Zoom), and revealed that the telehealth approach was feasible, safe, and well-accepted among older adults, particularly in relieving

